##### Oxygen Saturation

Pulse oximetry is widely used for patients who need continuous monitoring of Spo_2_. Its main purpose is the early detection of hypoxemia in various situations and the monitoring of perfusion and circulation; monitoring is non-invasive (Diccini et al., 2011). Before starting therapy with VR and conventional therapy, Spo_2_ will be measured. At the end of the respective therapies, Spo_2_ will be checked again.

##### Respiratory Rate and Heart Rate

Respiratory rate (RR) and HR will be measured before starting and at the end of both VR and conventional interventions.

### Blinding

The statistical analyst will be blinded throughout the treatment; i.e., the statistician will only know that there is a Group A and Group B carrying out the evaluations without information of what the treatment is, so that treatment of data is impartial.

### Assessment Protocol

The assessment protocol will have the following sequence. The functional scale (Barthel Index) will be undertaken first to ensure balance in randomization as this is a key variable. This is followed by group randomization process. After that, assessment scales will be undertaken in a separate room (BRUMS, MRC, and TUG) and one physiological assessment (HRV). The assessment part of the protocol will take around 1 h.

Borg Scale, Spo_2_, RR, and HR will be evaluated before and after each intervention. At the end of each day, ES and VASS questionnaires will be used to determine the individual's final perception of the intervention.

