According to Bond et al. (2019), the requirement of physical exercise inherent to a video game's activities (exergames) is shown to have a promising impact in improving patient self-efficacy for exercise training using digital hardware (e.g., the Nintendo Wii® or the Xbox Kinect®), once interactive VR promotes increased heart rate (HR), rating of perceived exertion (RPE), and physical activity (Bond et al., 2019; García-Bravo et al., 2019). Therefore, patients using exergames rather than conventional exercise routines (e.g., walking, running, or cycling) have been reported to exercise for longer periods, meeting moderate to vigorous physical activity levels, with the perception of “work” being lower or less intense, and more enjoyable, contributing to healthier lifestyle initiatives (Glen et al., 2017; Gomez et al., 2018; Polechoński et al., 2019).

Considering the above deliberations, we have organized a randomized controlled crossover protocol to investigate rehabilitation of patients hospitalized with COVID-19. The aim of this protocol is to find out whether the motor performance, functionality, engagement, motivation, and physiological parameters are different during conventional or virtual intervention. We are interested in comparing conventional cardiovascular and musculoskeletal physical therapy interventions with typical movements and mobilization in different postures such as sitting and standing, using VR software that provides a game in which the participants continually move upper limbs and trunk to finish a motor task proposed by the application. Participants will therefore alternate their rehabilitation intervention (conventional or virtual) during their hospitalization period. Furthermore, we will be using a satisfaction scale to verify the level of engagement in the therapy during the rehabilitation program.

We hypothesize that all participants will show improvement in motor performance, functionality, and physiological parameters independent of the intervention (conventional or virtual environment); however, the use of a virtual task will provide more engagement and motivation. If our hypothesis is proven, it might be the beginning of a technological innovation in cardiorespiratory rehabilitation in hospitals.

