##### Enjoyment Scale

An enjoyment scale using smiley faces (0 is “not fun at all,” 1 is “boring,” 2 is “a bit of fun;” 3 is “fun,” and 4 is “great fun”) will be applied after the end of the game sequences, as the motivation may be related to the motor proficiency level.

This scale was developed by Jelsma et al. (2014) to evaluate how people feel when interacting with proposed non-immersive VR games. It was used in other studies using different games (Farhat et al., 2016; Smits-Engelsman et al., 2017) and by da Silva et al. (2020a) with the same game used in this study. In the present study, the scale will be applied in the first and last days of the protocol to verify the participant's level of satisfaction with the games presented.

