##### Visual Analogical Satisfaction Scale

The 10-cm VASS assesses the level of satisfaction of the interviewed individuals. Patients will answer the questionnaire and be asked to mark a vertical line on the scale indicating satisfaction with rehabilitation, where zero (0) indicates very dissatisfied, and 10 indicates very satisfied (Brokelman et al., 2012; Voutilainen et al., 2016).

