### Procedure

Immediately before the beginning of each therapy (virtual intervention or conventional intervention), two assessment scales will be made (BORG Scale, Visual Analog Scale) and four physiological assessments [HRV, Spo_2_, RR, and HR]. Group A will start the first day of the protocol with virtual intervention (in the morning) and then in the second period (in the afternoon) will perform the conventional intervention, and Group B will perform the reverse protocol, in a crossover format. It will be applied for up to 8 consecutive days. On the last day, assessment scales will be repeated in a separate room, as well as the physiological assessments. After 7 days and 1 month of hospital discharge, all assessment scales will be undertaken at patients' homes, and the virtual intervention will be applied again (Figure 2).

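### With enjoyment and satisfaction rated at the end of each day, after both therapies, the ES and VASS schedule does not identify a virtual-versus-conventional difference

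*Protocol article*

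**What the plan says.** The Introduction expects motor, functional and physiological gains whichever therapy is used, and then makes its one directional prediction: "however, the use of a virtual task will provide more engagement and motivation". It names the instrument: "we will be using a satisfaction scale to verify the level of engagement in the therapy". The Secondary Outcome section lists satisfaction and enjoyment. The Statistical Analysis section puts ES and VASS among the dependent variables to be compared between virtual and conventional therapy, both between groups and within the same subject.

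Under Overview of the Study Design, both groups receive both therapies on the same day, one in the morning and one in the afternoon. Only the order differs.

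The timing of the two scales is stated in several places:

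- **Assessment Protocol:** "At the end of each day, ES and VASS questionnaires will be used to determine the individual's final perception of the intervention". The sentence just before it places Borg, SpO2, respiratory rate and heart rate before and after each intervention.
- **Visual Analogical Satisfaction Scale:** the patient marks a line "indicating satisfaction with rehabilitation", with no therapy named.
- **Enjoyment Scale:** ES "will be applied after the end of the game sequences", and "the scale will be applied in the first and last days of the protocol".
- **Procedure:** immediately before each therapy "two assessment scales will be made (BORG Scale, Visual Analog Scale". This section does not say that the visual analogue scale is the VASS.
- **Table 1:** ES and VASS are marked on each of days 1 to 8 and at both post-discharge visits.

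**The concern.** To test whether one therapy engages patients more than the other, each therapy needs its own score. A crossover with both therapies every day is well placed to give one, because each patient can act as his or her own control. A rating taken once both sessions are over, about rehabilitation in general, gives that advantage away: it is a single number for the pair.

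At stake is the one domain in which the article predicts a difference, and one of the two questions that its Discussion sets out to answer. Ratings that were never taken separately cannot be recovered by any later analysis, so this has to be settled in the conduct of the trial and not in an analysis plan. The competing timings add a second risk: sites or assessors who follow different sections will collect different data under the same scale name.

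**Working it through.** **Inputs.** Both therapies every day, order reversed between groups (Overview of the Study Design; Intervention). One end-of-day assessment (Assessment Protocol). 2 to 8 treatment days (Intervention). 40 patients, 20 per group, before the withdrawal allowance, and d = 0.65 (Recruitment). The article gives d = 0.65 for its motor score; it is borrowed here only to illustrate size. The article gives no figure for ES or VASS that could be reproduced.

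**1. Is the contrast estimable from one end-of-day rating?** Write the rating as intercept + effect of virtual therapy received + effect of conventional therapy received + effect of order. Every patient-day has virtual = 1 and conventional = 1, so the rows are (1, 1, 1, 0) for one group and (1, 1, 1, 1) for the other. The matrix has rank 2 with 4 columns. Adding the contrast (0, 1, −1, 0) raises the rank to 3, so virtual minus conventional lies outside what the data can estimate. More days or more patients only repeat the same two rows.

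**2. What does Group A versus Group B measure?** Let V and C be the responses to the two sessions, and let the patient weight the afternoon by w and the morning by 1 − w (an assumption; the documents give no value).

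- Group A (virtual in the morning): (1 − w)V + wC
- Group B (conventional in the morning): (1 − w)C + wV
- A − B = (1 − 2w)(V − C)

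With V − C = 0.65 SD and 20 per group (two-sample t, two-sided 0.05):

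| w | A − B (SD) | Power |
|---|---|---|
| 0.3 | +0.26 | 0.13 |
| 0.4 | +0.13 | 0.07 |
| 0.5 | 0 | 0.05 |
| 0.6 | −0.13 | 0.07 |
| 0.7 | −0.26 | 0.13 |
| 1.0 | −0.65 | 0.52 |

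The sign itself turns on w. If the order were switched on later days, a comparison between days would carry the same factor (1 − 2w).

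**3. Do the other sections supply the missing rating?**

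- *Enjoyment Scale:* a score after the game belongs to virtual therapy, but no matching score after conventional therapy is specified. First and last days only also contradicts the daily schedule.
- *Procedure:* a rating before a session is not a rating of that session. If the scale were the VASS, the day-1 rating before the afternoon session would follow the morning therapy alone and permit a randomised A-versus-B comparison. That comparison is not planned, and the identity of the scale is not stated.
- *Table 1:* it cannot settle the number of ratings. Borg, oxygen saturation, respiratory rate and heart rate also carry one mark per day, although they are taken before and after each session. A mark shows the day of collection only.
- *Post-discharge visits:* only the virtual intervention is applied again (Procedure), so ratings there have no conventional partner.

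**4. What would one rating per session give?** The columns are intercept, period and therapy. The four group-by-session rows are (1, 0, 1), (1, 1, 0), (1, 0, 0) and (1, 1, 1), with rank 3 of 3. Let δ be virtual minus conventional and π be afternoon minus morning. The within-day difference has mean δ − π in Group A and δ + π in Group B, and the average of the two group means is δ. This assumes that the morning session does not carry over into the afternoon rating.

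Each patient would contribute 2 to 8 pairs. One pair from each of 40 completers gives 80% power (two-sided 0.05) at a standardised within-patient difference of about (1.960 + 0.842)/√40 = 0.443 by the normal approximation, or 0.454 by the paired t-test. This describes the repaired design, not the size of the flaw. For ES, a 0-to-4 ordinal item, it is only approximate.

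**The case against.** The strongest reply is that the Assessment Protocol fixes when the forms are given, not how many are filled in. Two forms at the end of the day, one for each therapy, would fit its wording. The Secondary Outcome and Statistical Analysis sections suggest that scores for each therapy were intended, and the wording of forms is often left to a fuller protocol that is not shown. This stands in part: a single joint form is not proved to be the intention. But no section mentions two forms, the VASS wording is general, and the same section puts other measures around each session and these two at day's end.

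A reader might also infer four stronger things that the documents do not support:

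- *That the engagement hypothesis cannot be tested at all.* The check shows non-identification under the end-of-day schedule. The Procedure section might allow an unplanned day-1 comparison if its scale is the VASS.
- *That no rating belongs to one therapy.* ES after the game, and the ratings at the post-discharge visits, attach to virtual therapy. What is missing is a specified conventional counterpart.
- *That Table 1 confirms one rating per day.* It shows days, not counts.
- *That a recency effect will pass for a virtual-reality effect.* That is one scenario. The weight is unknown, and the A-versus-B difference could be positive, zero or negative.

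Finally, these are secondary outcomes, and the Primary Outcome section concerns the autonomic nervous system. That limits the reach of the problem. It does not alter the fact that the article's one directional prediction rests on these scales.

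**Conclusion.** The point holds for ES and VASS as scheduled in the Assessment Protocol section. Followed as written, that section yields ratings that cannot separate virtual from conventional therapy, either within patients or between groups. Group A versus Group B then reflects session order only: a true 0.65 SD difference could appear anywhere from +0.26 to −0.26 SD as the afternoon weight runs from 0.3 to 0.7, and a larger sample does not cure that. The result rests on reading the end-of-day assessment as one rating of the day; the weights and the 0.65 SD are illustrative. The Enjoyment Scale and Procedure sections conflict with that schedule and with each other's approach, and neither supplies a planned paired rating. The conflict in timing holds whichever reading is taken.

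**What to change.** Reconcile Table 1 with the Enjoyment Scale, Assessment Protocol and Procedure sections so that there is one rule. During hospitalization, give ES and VASS immediately after every virtual and every conventional session, with wording that refers to the session just completed. Remove the end-of-day, first-and-last-day-only and before-therapy timings for these two scales, and state whether the visual analogue scale in the Procedure section is the VASS. Mark Table 1 to show collection after each session.

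In the Statistical Analysis section, specify the paired within-day virtual-minus-conventional difference, adjusted for morning or afternoon, as the analysis of ES and VASS. Report the ratings at 7 days and 1 month after discharge descriptively and outside this contrast, because only virtual therapy is applied there.

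The cost is one extra administration of two short scales per day, plus the change of wording. Days already completed under an end-of-day rating cannot be converted into pairs.

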### Intervention

After performing all the tests and questionnaires of the initial evaluation, the individuals will be divided into two groups: Group A: participants with COVID-19 who will start the first day of the protocol with virtual intervention and then in the second period will perform the conventional intervention (*n* = 25); and Group B: participants with COVID-19 who will start the first day with conventional intervention and in the second period will perform activity with VR intervention (*n* = 25). After the application of therapies, final evaluations will be carried out. The rehabilitation protocol will be applied during hospitalization, for 2–8 consecutive days, unless they withdraw from the study—the number of days may vary due to length of hospitalization.

Participants will perform the tasks individually in the hospitalization sector, in the presence of the evaluator responsible for providing the intervention and recording the results, considering the patient's general condition. According to the recommendations of the European Respiratory Society, conventional physiotherapy includes (1) mobilization: referring to physical activity sufficient to elicit acute physiological effects that enhance ventilation, central and peripheral perfusion, circulation, muscle metabolism, and alertness and are countermeasures for venous stasis and deep vein thrombosis; and (2) respiratory therapy: to improve global and/or regional ventilation and lung compliance and to reduce airway resistance (Gosselink et al., 2008).

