Key inclusion and exclusion criteria	Inclusion criteria: Agreement to participate in the research from themselves by signing consent form, a clinical and posterior blood analysis of COVID 19 infection, adults with age ranging from x to xx years. Exclusion criteria: Do not understand the tasks; the understanding of the task will be evaluated through five attempts at each task in virtual reality; do not want to use virtual reality task; was not in a physical condition to practice a functional task; use of an intravenous device that makes it impossible to move the arms; cardiac arrhythmias and atrioventricular block; congenital anomalies, such as congenital heart defects, pulmonary malformations; and patients who use drugs that interfere with ANS, such as antiarrhythmic agents
Study type Interventional allocation	Randomized
Masking	Randomization and data analyst
Assignment	Crossover
Primary purpose	Treatment
Date of first enrolment	June 2020
Target sample size	50
Recruitment status	Recruiting
Primary outcome(s)	Functional capacity improvement
Key secondary outcome(s)	HRV improvement

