### Overview of the Study Design

A randomized controlled crossover protocol will be conducted, and all participants will undertake interventions in non-immersive VR–virtual intervention (with a serious game in web platform) and conventional intervention (with cardiovascular and musculoskeletal conventional physical therapy). All participants will be randomly divided in two groups: Group A will start the first day of the protocol with virtual intervention in the morning (their first rehabilitation session of the day) and the conventional intervention in the afternoon (their second rehabilitation session of the day). Group B will perform the reverse protocol (i.e., starting the first day of the protocol with conventional intervention in the morning and the virtual intervention in the afternoon) in a crossover design, during the hospitalization period (varying from 2 to 8 days according to individual needs). We chose two interventions per day, as it is the protocol of the Hospital of the Federal University of São Paulo (Hospital São Paulo) for inpatients in ambulatory unit.

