### Randomization

Participants will be randomly allocated to either Group A or Group B with a 1:1 allocation defined by a website (randomization.com). As we will have the participant's characteristics, immediately after the randomization the age and functional capacity (Barthel Index) will be compared between groups. If the groups are not homogeneous, a new randomization will be carried out. This protocol will be repeated until there is no difference between age and Barthel Index among groups (in a maximum of first three attempts at randomization, we always have homogeneous groups). Randomization will be under the control of a blinded investigator who will be the only person allowed to manage the electronic security file of the randomization to locate the individuals. The investigator applying the interventions will then be informed about which group the participant was allocated to so they can conduct the protocol in the correct order of interventions.

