### Virtual Intervention

During the protocol, the participants will perform tasks in a non-immersive VR environment for 10 min. Thus, we will use the MoveHero game (for details and publication, see Martins et al., 2019) that provides mobilization exercises to activate the upper and lower limbs, orthostatic training, and static and dynamic balance. The software that will be used was developed by the Research Group and Technological Applications in Rehabilitation group from the School of Arts, Sciences, and Humanities of the University of São Paulo and can be accessed at www.movehero.com.br/en.

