### Statistical Analysis

Statistical analysis will be performed using IBM-SPSS (version 26.0, IBM Corp., Armonk, NY, USA). As dependent variables, all HRV indices will be considered, as well as test scores of Barthel Index, TUG, MRC, BRUMS, ES, VASS, Borg Scale, Sao_2_, RR, and HR. If the data meet the assumptions of normality, multiple analysis of variance will be used to compare the study groups (virtual group and conventional group) and intragroup comparison (virtual and conventional groups, when comparing the same subject), with least significant difference *post-hoc* test. If the data do not meet the assumptions of normality, the differences between the groups will be analyzed using the Kruskal–Wallis test. Dunn *post-hoc* tests will be performed on each pair of groups, with Dunn–Bonferroni post-test on each pair of groups. The same tests will be applied for *p* < 0.05, which will be considered significant.

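### One unblinded evaluator delivers and records each session, and masking the analyst to Groups A and B is not shown to mask VR versus conventional

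*Protocol article*

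**What the plan says.** All references are to the protocol article.

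- **Delivery and recording.** Under Intervention, patients carry out the tasks "in the presence of the evaluator responsible for providing the intervention and recording the results".
- **Knowledge of allocation.** Under Randomization: "The investigator applying the interventions will then be informed about which group the participant was allocated to".
- **Who is masked.** The masking row of Table 2 reads "Randomization and data analyst". It lists no patient, therapist or outcome assessor.
- **What the analyst sees.** Under Blinding, "the statistician will only know that there is a Group A and Group B", and works "without information of what the treatment is, so that treatment of data is impartial".
- **What A and B are.** Under Overview of the Study Design, Group A has VR in the morning and conventional therapy in the afternoon, and "Group B will perform the reverse protocol". Every patient receives both.
- **What is compared.** Statistical Analysis sets out to "compare the study groups (virtual group and conventional group"), and adds a within-subject comparison of the two.
- **Expected direction.** The last paragraph of the Introduction expects motor, functional and physiological gains whichever therapy is used, but more engagement and motivation with VR.
- **Origin of the game.** Under Virtual Intervention, the software is described as "developed by the Research Group and Technological Applications in Rehabilitation group from the School of Arts, Sciences, and Humanities of the University of São Paulo". Table 2 names the same university as primary sponsor.

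**The concern.** The patient knows which therapy was given, and so does the person who gave it and writes down the results. Self-reports can drift towards what the patient thinks the therapist hopes to hear, and recorded values can drift towards what the recorder expects. The one directional prediction, that VR engages and motivates more, is tested on outcomes of this kind. That the game comes from the sponsor's own university implies no misconduct, but it is a further reason to protect the measurement.

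The protocol offers analyst masking as its assurance of impartial data handling. If that masking covers session order but the analysis file labels sessions as virtual or conventional, the assurance does not reach the comparison being made. A favourable VR result on the subjective scales could then not be separated from reporting bias.

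**Working it through.** The plan states no figure on this point, so the check is mainly textual, with one piece of algebra.

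**1. Who is aware of session type during data collection?** The patient (one session is a game), the therapist-evaluator (told the allocation and delivering the session), and no independent assessor who might not be.

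**2. Which outcomes does this reach?**
- *Borg and respiratory rate* are taken before and after every session (Assessment Protocol; Respiratory Rate and Heart Rate). On the natural reading of the Intervention section, the evaluator records them. They are exposed session by session.
- *Enjoyment and satisfaction* are self-reports. Assessment Protocol puts both at the end of the day, after both sessions. The Enjoyment Scale section ties that scale to the game and to the first and last days, Table 1 marks both scales daily, and Procedure places a visual analogue scale before each therapy. They are exposed if this evaluator collects them, but a per-session VR-versus-conventional contrast is not clearly defined for them.
- *BRUMS, MRC, TUG and resting HRV* are done in a separate room (Assessment Protocol; Procedure). The assessor is not stated, so nothing can be concluded about that person.
- *HRV* comes from a chest strap with beat-by-beat capture, filtered in software. Judgement enters in choosing 1,000 consecutive intervals from a 20-minute record and in the filtering.

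**3. Can A/B masking hide VR versus conventional?** Let d be a patient's morning value minus the afternoon value, τ the VR-minus-conventional effect and π the morning-minus-afternoon effect.
- Group A (VR first): expected d = π + τ
- Group B (conventional first): expected d = π − τ
- Estimate: (mean d in A − mean d in B) / 2, which has expectation τ

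Swapping the two letters gives −τ with the same precision. In one simulated data set with 25 patients per order, the estimate was +0.521 with the true letters and −0.521 with them swapped. An analyst can therefore run the comparison without knowing which therapy it favours, on two conditions: (a) session records carry only time of day or another neutral code, and (b) the letters do not reveal the order.

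**4. Does the article meet those conditions?**
- (a) is not stated. Statistical Analysis names its groups virtual and conventional.
- (b) fails if the published letters are used unchanged, because the Abstract, Table 2, Overview of the Study Design and Intervention all define Group A as VR first.

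The Blinding and Statistical Analysis sections are thus not reconciled. They could be, with a coding step that the article does not describe.

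**The case against.** The strongest reply is that the protocol does claim a blinded statistician who does not know the treatment, and that in a two-sequence crossover hiding the order does hide the therapy. Step 3 of the working confirms this. How session data are coded may also sit in the full protocol. This part stands: the masking is not shown to fail, it is only not shown to hold.

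Some stronger readings may tempt a reader, and the document does not support them:

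- *That nobody is blinded.* Table 2, Randomization and Blinding all state masking of randomization and the analyst.
- *That the analyst must see the VR label.* Neutral session codes are enough.
- *That HRV is as exposed as the ratings.* It is recorded by a device, the interval count is fixed, and no section says the therapist processes it.
- *That enjoyment and satisfaction are reported to the person who has just delivered the game.* Assessment Protocol has them at the end of the day, when Group A's most recent session is conventional.
- *That the evaluator gives every scale.* The separate-room assessor is not named.

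It is also fair that VR cannot be concealed from patients, that they already mark the satisfaction line and answer BRUMS themselves, and that the monitor already captures heart rate throughout. No remedy removes the patient's own expectation. None of this removes the dual role of the evaluator or the unreconciled wording on A and B.

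**Conclusion.** The concern holds in a limited form. An evaluator who knows the allocation delivers the sessions and records their results, with no blinded assessor named. Borg, respiratory rate and any enjoyment or satisfaction rating this person collects are exposed to expectation and courtesy bias, which for engagement would favour VR. The stated analyst masking concerns session orders that the article itself decodes, and it is not shown to cover virtual versus conventional. HRV is less exposed.

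No size can be put on the bias. The document gives no spread for the subjective scales and no clear per-session contrast for enjoyment or satisfaction, and the planning effect of 0.65 under Recruitment belongs to the motor score, so it is no yardstick here.

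The conclusion rests on reading the results in the Intervention section as including the measurements taken around each session. It ranks as a cheap improvement and does not invalidate the design.

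**What to change.** 1. Have patients complete the Enjoyment Scale, VASS, BRUMS and Borg themselves, on a form that is then sealed or on a tablet, without the evaluator reading or prompting. Note any patient who needs help.
2. Take pre- and post-session heart rate from the Polar record already collected, instead of the evaluator's note.
3. Replace both the A/B letters and the VR/conventional labels with neutral session codes, with the key held by the investigator who controls randomization. Keep the codes in place through HRV segment selection, filtering and analysis.
4. Amend the Blinding section to say that session type is what is masked.

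The cost is form handling, one recoding step and reading help for some frail patients. No extra assessor is needed. Respiratory rate stays exposed if the evaluator counts it, and that should be stated as a limitation.
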